## Abstract

**Introduction:**

Glaucoma is the leading irreversible blinding eye disease worldwide and the global prevalence of glaucoma for individuals aged 40–80 years is estimated as 3.54%. Early screening and prevention wherever possible are essential interventions of chronic disease management for glaucoma, but there is currently a lack of a recognized glaucoma screening model for Chinese population. Therefore, this study intends to construct and validate an artificial intelligence (AI)-assisted three-tiered glaucoma screening model based on the community population and assess its cost-effectiveness.

**Methods and analysis:**

This is a community population-based cluster randomized controlled trial with a minimum of 6-year follow-up. A three-tiered glaucoma screening strategy appropriate for Chinese individuals will be established, including a high-risk model questionnaire (primary screening), ophthalmic examinations (secondary screening, combined with physician-based and AI-assisted image interpretation), and definitive diagnosis by tertiary hospitals (tertiary screening). The participants of each community will be randomly divided into three groups (simple cluster randomization): no screening group, routine screening group, and tiered screening group. Participants in the no screening group will receive regular glaucoma-related health education, structured annual follow-up for symptom monitoring and recording of external ophthalmology visits, and a comprehensive ophthalmic screening at the end of the study to compensate for the absence of regular screening. A total of 28,275 participants (9,425 per group) will be recruited, allowing for an anticipated loss-to-follow-up rate of 20%. All primary outcome measures will be analyzed on a per-participant basis. The main endpoint is the glaucoma detection rate, with sensitivity and specificity of the screening as additional primary outcomes. Secondary outcomes involve comparative analyses of the cost-effectiveness of different screening strategies and the diagnostic accuracy of physician-based versus AI-assisted image interpretation.

**Ethics and dissemination:**

The protocol has been approved by the Biomedical Ethics Review Committee, West China Hospital of Sichuan University [2025(1021)]. All the participants will be required to afford signed informed consent. The study results will be presented at scientific meetings and published in a peer-reviewed journal.

**Clinical trial registration:**

https://www.chictr.org.cn/showproj.html?proj=281642, identifier (ChiCTR2500107852).

## Introduction

1

Glaucoma is the leading cause of irreversible blinding worldwide and continues to threaten global visual health. The global prevalence of glaucoma among adults aged 40–80 years is estimated to be 3.54%, affecting approximately 80 million people (1, 2). Of these, 10% of patients with primary open-angle glaucoma (POAG) and 25% of those with primary angle-closure glaucoma (PACG) are bilaterally blind (3, 4). In China, the number of glaucoma patients has surpassed 21 million, the highest of any country, and more than 70% of cases are diagnosed at intermediate or advanced stages, or even after monocular blindness has already occurred (5). With population aging, the burden of glaucoma continues to rise. The deterioration in quality of life caused by visual impairment exceeds that associated with many other forms of disability, and glaucoma-related visual loss diminishes the capacity for independent mobility and daily living (6), which in turn has direct and indirect consequences for socioeconomic development and increases the national healthcare burden. Indeed, glaucoma is a critical public health challenge in an aging society.

Although the visual function damage caused by glaucoma is irreversible, it can still be prevented and controlled through early detection (4). If primary glaucoma, including POAG and PACG, is detected and diagnosed before the onset of subjective symptoms, timely and effective intraocular pressure (IOP)-lowering treatment can avoid blindness and substantially alleviate the burden on patients. Nevertheless, owing to the insidious nature of early-stage glaucoma, most patients are already at moderate or advanced stages when first diagnosed. Previous data from China showed that at initial diagnosis, 25% of patients had visual acuity worse than 0.3 (Snellen equivalent of 20/63), and 15% had already progressed to monocular blindness (7, 8). Therefore, early screening, early prevention, early diagnosis, and early treatment are essential components of chronic disease management for glaucoma.

However, a universally recognized glaucoma screening model is still lacking. Low screening uptake, high costs, and heavy reliance on specialist physicians remain the principal barriers to effective screening (9). Consequently, how to define the target population for screening (more accurate screening population) and which screening protocol to adopt (more feasible) are important questions that warrant further investigation. In developed countries, where POAG is the predominant form (3, 10) and is characterized by a relatively low incidence, gradual progression, and a diagnostic process often requiring comprehensive examinations, high primary eye care coverage, well-established referral pathways from optometrists to ophthalmologists, and generally lower population density facilitate more efficient healthcare delivery with less resource dispersion. Under these conditions, screening targeting high-risk groups is preferred over population-based screening, as the latter has been shown to be less cost-effective (11). For instance, annual glaucoma screening for high-risk populations has been incorporated into health insurance in the United States, contributing to a reduction in glaucoma-related blindness (12). In contrast, in developing countries and economically disadvantaged regions, limited medical resources are largely allocated to treating patients with intermediate and advanced glaucoma. In China, given the high population density and insufficient primary eye care coverage, implementing population-wide screening for chronic diseases at the community level is therefore particularly crucial.

At present, despite the fact that the Chinese Glaucoma Guideline (2020) has recommended slit lamp microscopy, IOP measurement, and fundus examination as routine glaucoma screening methods (5), the cost-effectiveness of these approaches in screening remains uncertain. Consequently, there is also an urgent need to develop a glaucoma screening model that is cost-effective, scalable, and suited to the national context. Furthermore, rapid economic and technological advances have facilitated the widespread adoption of telemedicine and artificial intelligence (AI), offering innovative approaches to glaucoma screening (13). Specifically, AI-assisted diagnosis and follow-up can markedly improve screening efficiency and quality, reduce dependence on specialists, and save considerable time and financial resources, potentially leading to a more effective, convenient, and cost-effective screening model (14–17).

Therefore, this study intends to conduct a cluster randomized controlled trial with a 6-year follow-up to establish and validate an AI-assisted three-tiered glaucoma screening model based on the community population, assess its cost-effectiveness, and evaluate the performance of AI-assisted diagnostic tools, thereby generating evidence to inform future optimization.

## Methods and analysis

2

### Objectives

2.1

Main objectives: (1) To construct and validate a three-tiered glaucoma screening model based on the community population; (2) Preliminary evaluation of the cost-effectiveness of the screening model to provide basic data for subsequent in-depth health economics analysis.

Secondary objectives: (1) To develop an evaluation tool of screening for populations at high risk of glaucoma; (2) To evaluate the application effect of AI-assisted diagnostic tools to provide a basis for subsequent optimization.

### Study design

2.2

This is a community population-based cluster randomized controlled trial with a 6-year follow-up conducted in several community healthcare centers in Yibin City, Sichuan Province, China. This study will commence with the construction and validation of a preliminary glaucoma screening tool to identify high-risk populations in China. The initial phase involves the formation of a comprehensive item pool through a systematic literature review focusing on glaucoma risk factors, early symptoms, and existing screening instruments, supplemented by structured discussions with glaucoma specialists to capture clinically relevant indicators not fully reflected in the published literature. Integrating evidence from both sources, an initial item pool will be constructed, covering domains such as clinical presentations, medical and family history, medication use, lifestyle habits, and glaucoma awareness.

Subsequently, a Delphi expert consultation process will be conducted with 10–15 national glaucoma specialists representing clinical, epidemiological, and public health expertise. Over 2–3 rounds of anonymous scoring and feedback, panelists will rate each candidate item on importance, relevance, and feasibility using a five-point Likert scale. Item retention will be guided by predefined threshold criteria based on mean importance scores, full-score frequencies, and coefficients of variation. Specifically, items with a mean score ≥ the average, a full-score frequency ≥ the average, and a coefficient of variation ≤ the average will be retained. Additional refinement through expert consensus will be applied to merge redundant items and clarify ambiguous wording. After adaptation for linguistic accessibility and clinical applicability, the final set of items will be determined upon completion of the Delphi process.

Finally, the refined tool will undergo final item selection and rigorous reliability and validity testing using cross-sectional data from the Ophthalmology Department of West China Hospital, Sichuan University. As a result, the finalized screening tool (a well-designed questionnaire) will be determined and employed for screening within the target population in this study.

This screening tool will underpin a proposed three-tiered strategy for glaucoma screening. Tier 1 Screening (Primary Screening): The pre-designed risk assessment questionnaire is administered within the community to identify high-risk individuals. Tier 2 Screening (Secondary Screening): These high-risk individuals undergo a combination of screening tests, including visual acuity, IOP measurement, fundus photography, and ocular optical biometry, which will be conducted at community healthcare or primary care centers. This stage is augmented by AI-assisted image interpretation to identify subjects suspected of having glaucoma. Tier 3 Screening (Tertiary Screening): A definitive diagnosis of glaucoma is established within the ophthalmology department of a tertiary hospital.

In the Tier 2 screening stage, fundus photographs will be interpreted using the Airdoc glaucoma-specific AI automatic screening system, which is built on a deep convolutional neural network algorithm employing an integrated multi-task learning architecture for simultaneous segmentation and classification. Standardized and traceable glaucoma grading decision rules have been established and fully integrated into the screening workflow. The system automatically performs image preprocessing, precise optic disc detection, quantitative analysis of optic disc morphology, segmentation of the optic cup and retinal nerve fiber layer defect (RNFLD) regions, and identification of glaucomatous lesions including localized RNFLD, diffuse RNFLD, optic disc hemorrhage, and optic cup notching. Moreover, it also calculates horizontal and vertical cup-to-disc ratios, ultimately generating a quantitative glaucoma risk score and a graded recommendation.

This AI system has been trained and internally validated on a large-scale fundus image dataset from Chinese PLA General Hospital, achieving a mean area under the receiver operating characteristic curve (AUC) of 0.941 for optic disc segmentation, 0.874 for optic cup segmentation, and 0.893, 0.901, 0.969, and 0.892 for the classification of the four aforementioned lesions, respectively (18). It has undergone independent external dataset validation and multicenter prospective clinical performance evaluation, with both algorithmic stability and generalizability systematically assessed. Within our screening workflow, all fundus photographs will first be independently interpreted by ophthalmologists at the level of attending physician or higher, while simultaneously undergoing automated image interpretation and risk stratification by the AI system. Then, the human and AI interpretations will be compared. In cases of disagreement, the images will be referred to a glaucoma specialist for final adjudication, and the specialist’s judgment will serve as the reference standard. This forms a standardized screening pattern combining AI-assisted initial screening with physician review for final confirmation.

All participants who enter the Tier 3 screening stage will undergo further examinations for definitive diagnosis, including standard automated perimetry for visual field testing, optical coherence tomography (OCT) imaging of retinal nerve fiber layer (RNFL) thickness, and gonioscopy to distinguish open-angle from angle-closure glaucoma. The final diagnosis will be made independently by two glaucoma specialists following a comprehensive review of all clinical data, with reference to internationally accepted diagnostic criteria for glaucoma, namely the presence of characteristic glaucomatous optic neuropathy with corresponding visual field defects, after excluding other ocular or neurological conditions that may cause optic neuropathy. Any diagnostic disagreement between the two specialists will be resolved by a third senior glaucoma expert who will make a final determination. To correct for verification bias, a random sample of 10% of participants who are screen-negative will also be recalled to undergo the same reference standard examination. Sensitivity and specificity of the two screening strategies will be calculated based on all screen-positive participants and the randomly selected screen-negative subset, with appropriate weighting to account for the sampling fraction.

The study is scheduled to begin patient enrollment in October 2025, with follow-up and final data collection expected to be completed in December 2032.

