### Follow-ups and outcome variables

2.6

Commencing at study initiation, participants will be prospectively followed up annually for a minimum of 6 years. Data will be collected yearly through IOP measurements, fundus photography, and follow-up questionnaires (Table 1). For patients with suspected or confirmed glaucoma, additional data will be collected including ocular optical biometry, RNFL thickness, and automated perimetry. Long-term follow-ups will track annual incidence and blindness rates of glaucoma, and quality of life among glaucoma patients.

**Table 1 tab1:** Follow-up schedule.

Groups		Visit number	0	1	2	3	4	5	6
		Visit time (year)	Baseline	1	2	3	4	5	6
No screening group		Questionnaire	×	×	×	×	×	×	×
Routine screening group		Questionnaire	×	×	×	×	×	×	×
		Intraocular pressure	×			×			×
		Fundus photography	×			×			×
Tiered screening group	High-risk population	Questionnaire	×	×	×	×	×	×	×
		Intraocular pressure	×	×	×	×	×	×	×
		Fundus photography	×	×	×	×	×	×	×
		Glaucoma specialist examination	Performed according to the screening results						
	Non-high-risk population	Questionnaire	×	×	×	×	×	×	×
		Intraocular pressure							
		Fundus photography							

All primary outcome measures will be analyzed on a per-participant (per-person) basis. The main endpoint of this study is glaucoma detection rate of the screening protocol, with sensitivity and specificity of the screening included as additional primary outcome measures. Glaucoma detection rate is defined as the proportion of participants in each arm with a final confirmed diagnosis of glaucoma in at least one eye, as determined by the reference standard examination in the screening arms or by passive case-finding through medical records in the control arm. Sensitivity is defined as the proportion of participants with confirmed glaucoma in at least one eye (as determined by the reference standard comprehensive ophthalmic examination) who are correctly identified by the screening protocol. Specificity is defined as the proportion of participants with no glaucoma in either eye who are correctly classified as negative by the screening protocol.

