Secondary outcome measures include comparative analyses of the cost-effectiveness of different screening strategies and the diagnostic accuracy of physician-based versus AI-assisted image interpretation in fundus photography for screening glaucoma. The comparison of diagnostic accuracy will be evaluated at the per-participant level and will include sensitivity and specificity, as well as AUC for each interpretation method.

The cost-effectiveness analysis will be conducted from a societal perspective to comprehensively evaluate the resources consumed and health outcomes generated by different screening strategies. The primary economic outcome is the incremental cost-effectiveness ratio (ICER), expressed as the incremental cost per additional glaucoma case detected (based on observed data within the study period), and the incremental cost per quality-adjusted life year (QALY) gained (based on long-term model extrapolation). Cost components will encompass screening-related expenses, including personnel, equipment, consumables, site costs, and AI-assisted interpretation fees; diagnostic confirmation costs following referral, such as OCT and automated perimetry; subsequent treatment and follow-up costs; and direct non-medical and indirect costs, including transportation expenses and productivity losses incurred by patients and their families. Health utility values will be measured prospectively among diagnosed patients during follow-up using the EQ-5D-5L instrument and converted to utility weights using the Chinese value set. Costs and effects within the study period will be obtained through actual data collection, whereas long-term outcomes will be evaluated using a Markov state-transition model simulating the natural history of glaucoma and the long-term trajectory following screening intervention. The model will employ a cycle length of 1 year and a lifetime horizon, and future costs and health outcomes will be discounted to present value at an annual rate of 3%. Uncertainty in the incremental analysis will be assessed through one-way sensitivity analyses and probabilistic sensitivity analysis, and cost-effectiveness acceptability curves will be generated to illustrate the probability that the tiered screening strategy is cost-effective across a range of willingness-to-pay thresholds.

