### Quality control, data management and supervision

2.7

The quality control and supervision of this study involve the following points:

(1) Prior to study initiation, standardized operating procedures (SOPs) are formulated for visual acuity testing, IOP measurement, fundus photography, and ocular optical biometry at community-based physical examination centers. All examiners will undergo standardized training on these protocols and are required to demonstrate competencies through formal assessment before being permitted to participate in the study.(2) The original data of examinations including visual acuity, IOP, and optical biometry will be retained for storage in the disease-specific database of the cohort study office, West China Hospital of Sichuan University. At least two researchers complete the form entry and checking work.(3) Fundus photographs are initially interpreted by experienced physicians holding a rank of attending physician or higher. Then, these assessments are compared with AI-based image analyses. Regarding discrepancy between the human and AI interpretations, the images will be referred to a glaucoma specialist for arbitration, with the expert’s judgment serving as the gold standard.(4) Automated perimetry and RNFL thickness measurements are served as definitive diagnostic tests, with all results being evaluated and confirmed by a glaucoma specialist whose judgment constitutes the gold standard.(5) All screening instruments and follow-up questionnaires would be reviewed by dedicated personnel. If there are incomplete filling out of forms or questionable responses, immediate follow-up contacts will be initiated for verification.(6) A central database is planned to be established and all data can be uploaded to the central database through the researchers in a timely manner, or directly through the inspection equipment via Internet.(7) The study involves a prolonged follow-up period, during which participant attrition is anticipated. The initial sample size calculation has taken an estimated loss-to-follow-up rate (20%) into consideration by expanding sample size. Furthermore, multiple strategies will be employed to enhance participant compliance, including simplifying questionnaire content to reduce response burden, shortening examination duration, and providing subsidies (financial support provided to cover or offset costs associated with the screening process, such as transportation expenses) as necessary. Additionally, active reattempts are made to contact participants lost to follow-up to determine reasons for withdrawal and minimize attrition wherever possible.

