Additionally, the cost-effectiveness analysis will adopt ICER as the economic evaluation measure, with estimated CIs using nonparametric bootstrapping. The sensitivity, specificity, and AUC of physician-based versus AI-assisted image interpretation will be calculated and compared, and differences in AUC will be assessed by the DeLong test or bootstrapping.

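### The physician-versus-AI accuracy comparison has no reference standard of its own except specialist review of discordant images, which would usually overstate the accuracy of both readers

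*Protocol article*

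**What the plan says.** Section 2.2 (Study design) describes independent reading of all fundus photographs by a physician and by the AI, after which the two readings are compared. The rule for discordant photographs is: "In cases of disagreement, the images will be referred to a glaucoma specialist for final adjudication". Of that adjudicator's opinion, the section says that the "judgment will serve as the reference standard". Section 2.7, item 3, repeats the rule: "Regarding discrepancy between the human and AI interpretations, the images will be referred to a glaucoma specialist for arbitration". The status given to this arbitration is again that of the truth, in the words "judgment serving as the gold standard". Neither section gives specialist image review to photographs on which the two readers agree.

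Section 2.6 lists as a secondary outcome "the diagnostic accuracy of physician-based versus AI-assisted image interpretation in fundus photography for screening glaucoma", evaluated per participant. Section 2.9 adds: "The sensitivity, specificity, and AUC of physician-based versus AI-assisted image interpretation will be calculated and compared". For the AUC contrast it leaves two methods open: "differences in AUC will be assessed by the DeLong test or bootstrapping". Neither section says what the readings are scored against.

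A second reference exists. In 2.2, the Tier 3 work-up (perimetry, OCT, gonioscopy, two specialists) is given to everyone who enters Tier 3 and to a random 10% of screen-negatives, with weighting for the sampling fraction. That passage ties it to the sensitivity and specificity of the two screening strategies. Section 2.6 likewise defines sensitivity of the screening protocol "as determined by the reference standard comprehensive ophthalmic examination". The reader comparison is not mentioned in either place.

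**The concern.** The only reference the article attaches to image reading is one that looks at disagreements. If an agreed reading is then taken as the truth, the reference is built largely from the two tests under evaluation. A case that both readers miss is scored as a correct negative for both, and a healthy eye that both flag is scored as a correct positive for both. Shared errors are plausible, because both readers see the same photograph.

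The article recognises verification bias and corrects for it in the strategy-level analysis, but it does not extend the correction to the readers. At stake are the secondary outcome on reader accuracy and the secondary objective of evaluating the AI tool, which the discussion hopes will feed into guidelines.

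**Working it through.** The article states no figure for the reader comparison. Its only sample size concerns the detection rate and does not bear on this point. All reader accuracies below are therefore assumptions.

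**Notation.** P is prevalence among the photographs read, *bm* the share of true cases missed by both readers, and *bf* the share of non-cases called positive by both. Agreement is taken as truth, and the adjudicator is error-free unless stated.

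- Reference positives = P(1 − *bm*) + (1 − P)*bf*
- Apparent sensitivity = [P × sens + (1 − P)*bf*] / reference positives
- Apparent specificity = [(1 − P) × spec + P × *bm*] / (1 − reference positives)

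**Set A (assumed).** P = 0.06; AI sensitivity/specificity 0.85/0.90; physician 0.75/0.93.

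*Independent errors:* *bm* = 0.15 × 0.25 = 0.0375; *bf* = 0.10 × 0.07 = 0.007.
- Reference positives = 0.05775 + 0.00658 = 0.06433
- AI sensitivity = (0.0510 + 0.00658)/0.06433 = 89.5% (true 85%)
- Physician sensitivity = (0.0450 + 0.00658)/0.06433 = 80.2% (true 75%)
- AI specificity = (0.8460 + 0.00225)/0.93567 = 90.7% (true 90%)
- Physician specificity = (0.8742 + 0.00225)/0.93567 = 93.7% (true 93%)

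*Partly shared errors:* *bm* = 0.10; *bf* = 0.02.
- Reference positives = 0.0540 + 0.0188 = 0.0728
- AI sensitivity = (0.0510 + 0.0188)/0.0728 = 95.9%, or 10.9 points too high
- Physician sensitivity = (0.0450 + 0.0188)/0.0728 = 87.6%, or 12.6 points too high
- AI specificity = (0.8460 + 0.0060)/0.9272 = 91.9%
- Physician specificity = (0.8742 + 0.0060)/0.9272 = 94.9%

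The true 10-point sensitivity gap becomes 9.3 points (independent) or 8.2 points (shared). The AI stays ahead, and the gap shrinks.

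**Set B (assumed accuracies; prevalence 3.54%, the figure used in 2.5).** Sensitivity 0.80 for the physician and 0.85 for the AI; both specificities 0.90.

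| Error correlation | Adjudicator sens/spec | Physician sensitivity | AI sensitivity | Specificity, physician / AI |
|---|---|---|---|---|
| 0 | 1 / 1 | 0.863 | 0.903 | 0.909 / 0.909 |
| 0.3 | 1 / 1 | 0.934 | 0.960 | 0.935 / 0.935 |
| 0.5 | 1 / 1 | 0.959 | 0.980 | 0.953 / 0.953 |
| 0.3 | 0.90 / 0.95 | 0.904 | 0.926 | 0.937 / 0.937 |
| 0 | 0.90 / 0.95 | 0.811 | 0.842 | 0.913 / 0.912 |
| 0 | 0.80 / 0.90 | 0.772 | 0.796 | 0.916 / 0.916 |

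The last two rows mark the limit of the claim. With independent errors and an imperfect adjudicator, sensitivity can fall below its true value: for the AI in the fifth row and for both readers in the sixth. Specificity is above 0.90 in every row.

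**Precision cost of the alternative.** Assume 3,000 photographs, Set A with shared errors, full verification of cases found by either reader, and 10% sampling of concordant negatives.
- Expected cases: 3,000 × 0.06 = 180. Missed by both: 180 × 0.10 = 18. Sampled: 18 × 0.10 = 1.8, each carrying weight 1/0.10 = 10.
- Standard error of AI sensitivity with every case verified: √(0.85 × 0.15/180) = 0.027.
- With the weighted sample, simulation gives 0.064.
- The chance that no jointly missed case is sampled is (1 − 0.06 × 0.10 × 0.10)^3000 = 0.165, about 17%.

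**The case against.** The strongest defence is that the adjudication rule is a workflow rule. In 2.2 it is presented as part of the screening workflow, and in 2.7 as quality control. The outcome in 2.6 is per participant and about screening for glaucoma, whereas adjudication is per image. The analysts may well intend the Tier 3 diagnosis as the reference, and if it is used with weights most of the bias goes. The article nowhere writes that concordant readings are accepted as truth. This stands: the bias follows from applying the text as it reads, not from an explicit statement. But the text calls the adjudication the reference and gold standard, offers nothing else for the readers, and reserves Tier 3 for the strategies.

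Four stronger readings are tempting and not supported:

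- **That the primary sensitivity and specificity are biased in the same way.** They use the Tier 3 reference with the weighted screen-negative sample.
- **That both readers' accuracy is certain to be overstated.** The last two rows of the Set B table show otherwise for sensitivity.
- **That the AUC contrast favours the AI because its score is quantitative and the physician's reading is yes/no.** No section says physicians record only yes/no. The AI also issues a graded recommendation, so grades could be compared.
- **That the plan commits to a DeLong test that ignores the verification weights.** Bootstrapping is already allowed in 2.9, and the weights matter only if Tier 3 is the reference.

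It is also fair that the comparison is relative. In Set A the ranking of the readers is preserved, so the harm lies mainly in the absolute accuracies and in a compressed difference.

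**Conclusion.** The point holds in a limited form. For one named secondary outcome, the only reference tied to image reading is specialist review of discordant photographs. If agreement is taken as truth, sensitivity and specificity will usually be inflated for both readers. In Set A the inflation of sensitivity is 4.5 points (AI) and 5.2 points (physician) with independent errors, and about 11 and 13 points with shared errors. These sizes rest on assumed prevalence, accuracies and error dependence. With an imperfect adjudicator and independent errors, even the direction for sensitivity is open. The primary outcomes stand. The change is worth making because the data that would remove most of the bias are already planned.

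**What to change.** State in 2.6 and 2.9 that the physician-versus-AI comparison uses the Tier 3 diagnosis as the reference for both readers. Restrict it to photographed participants: all screen-positives plus the random screen-negative sample, weighted by the inverse of the sampling fraction. The restriction matters because Table 1 schedules no photography for non-high-risk participants in the tiered arm, so any of them drawn into the 10% sample cannot inform reader accuracy. In 2.2 and 2.7, describe specialist review of discordant photographs as a referral step only, and remove its reference-standard and gold-standard labels. Of the two options in 2.9, choose the bootstrap, applying these weights and resampling communities.

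The cost is mainly wording, but the loss of precision is real. Each sampled case that both readers missed carries a weight of about 10, and in the example above the standard error of AI sensitivity rises from 0.027 to 0.064. The wider intervals should be accepted openly in the plan.
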